## Abstract

**Abstract:**

**Introduction:**

The international Surviving Sepsis Campaign guidelines highlight the need for recognising sepsis in a timely and accurate manner. Early diagnosis and treatment of sepsis are crucial and associated with reduced mortality. In the early stages of sepsis, heterogeneous clinical signs are difficult to interpret, often leading to missed or delayed diagnoses, as well as inappropriate or late use of antibiotics. There is an urgent need to quickly and accurately identify patients with potential infection in the emergency department (ED) who are at risk of progressing along the infection-sepsis spectrum. This study aims to compare the immune responses of ED patients presenting with a (suspected) infection, both with and without sepsis, to gain insights into immune aberrations and identify novel biomarkers linked to an increased risk of developing sepsis and its sequelae.

**Methods and analysis:**

A prospective observational cohort study across three hospitals in the Netherlands will be conducted. Adults presenting to the ED of these hospitals, with a (suspected) infection and a Modified Early Warning Score of 2 or higher, will be eligible for enrolment. We aim to include up to 3330 patients. The main study parameters will be characterisation of the host immune and metabolic response using multiomics analysis, Raman spectroscopy, mass spectrometry and gut microbiota profiling in relation to clinical outcomes such as 30-day mortality, length of hospital stay, readmission and postsepsis sequelae.

**Ethics and dissemination:**

Verbal and written informed consent will be obtained from all participants or their legal representatives. The study was approved by the Amsterdam University Medical Centre Ethics Committee (No. 2022.0279) and will adhere to the Declaration of Helsinki and the Medical Research Involving Human Subjects Act (WMO). Research results will be published in peer-reviewed journals.

**Trail registration number:**

ClinicalTrials.gov, NCT06178822.

STRENGTHS AND LIMITATIONS OF THIS STUDYBIOmarkers to diagnose SEPsis is a multicentre emergency department (ED) study providing insight into the early immune response in infection and sepsis.Broad inclusion criteria capture a wide range of infections, enabling differentiation between rapid recovery and critical illness.Integration of advanced analyses, including multiomics and microbiome profiling, allows exploration of biological processes beyond conventional biomarkers.Deferred consent enables inclusion of severely ill patients unable to provide consent at time of ED admission.Wide-ranging inclusion criteria may result in a low number of severe cases or confirmed infections.

## Introduction

 Sepsis continues to account for nearly 20% of all deaths worldwide, despite a global reduction in disease burden,^1^ and remains a major contributor to in-hospital mortality.^2^ The Surviving Sepsis Campaign has highlighted diagnosis as a critical challenge.^3^ Early diagnosis and treatment are crucial, as they are associated with lower mortality rates.^4^ However, in routine clinical practice, there is often a significant delay after admission before acting on the suspicion of a severe infection, such as administering antibiotics.^5^ In the early stages of sepsis, the infection source may be unclear, and clinical signs may be indistinguishable from those of non-infectious diseases, resulting in missed or delayed diagnoses.^6^

For over 25 years, patients with an infection who met two or more systemic inflammatory response syndrome (SIRS) criteria were diagnosed with sepsis.^7^ However, due to the limited specificity of the SIRS criteria, sepsis was redefined in 2016 to focus on the presence of organ failure, as measured by the sequential organ failure assessment (SOFA) score, in patients with a (suspected) infection.^4^ Since the SOFA score requires laboratory testing, the quick SOFA (qSOFA) score was introduced for early sepsis recognition at the bedside, based on three parameters: systolic blood pressure, respiratory rate and Glasgow Coma Scale. Unfortunately, many clinical scores, including qSOFA and the Early Warning Score, lack sensitivity and prognostic value in predicting sepsis and mortality.^8 9^ The most recent Surviving Sepsis Campaign guidelines recommend using SIRS, the National Early Warning Score (NEWS) or the Modified Early Warning Score (MEWS) as sepsis screening tools,^3^ with MEWS and NEWS being the most used.^10^ To address the limitations of clinical scores, several biomarkers have been evaluated, yet none have demonstrated sufficient specificity or sensitivity for routine clinical use.^11^,^13^ In addition, classical microbiological cultures are time-consuming and often yield negative results, further highlighting the absence of an ideal diagnostic tool for sepsis.^14^ The host response in sepsis is heterogeneous, with distinct biological subgroups identified in intensive care unit (ICU) cohorts, suggesting that a single biomarker is unlikely to enable accurate diagnosis.^15 16^ To address this complexity, multiomics approaches are needed, yet such strategies have rarely been applied in the emergency department (ED), particularly in the early stages of sepsis.^11^

Data from the USA indicate that sepsis is a common presentation in the ED and accounts for roughly one-third of all hospital admissions that result in death.^17^ Even after hospital discharge, patients initially admitted for sepsis continue to have an increased risk of death.^18^ US data showed that one-third of sepsis survivors die within the following year, with half of these deaths related to sepsis complications. Additionally, one-sixth of sepsis survivors experience severe, persistent physical disability or cognitive impairment.^19^ Consequently, the Surviving Sepsis Campaign guidelines now recommend assessing and observing the physical, cognitive and emotional health of patients after hospital discharge for sepsis.^3^ Although the challenges of critical illness survivorship are increasingly documented, there are still relatively few studies on enhancing recovery and identifying patients at increased risk for postsepsis health problems.^18^

There is a pressing need to rapidly and effectively identify ED patients at risk of progressing along the infection-sepsis spectrum. The objectives of the present study are (1) to compare the immune response of patients with and without sepsis presenting to the ED with (suspected) infection, (2) to identify immune response aberrations and biomarkers associated with an increased risk of developing sepsis in patients presenting to the ED with (suspected) infection and (3) to determine the long-term cognitive and physical sequelae of sepsis after hospital discharge.

We will investigate the immune response using transcriptomic, metabolomic and proteomic data to gain insights into sepsis pathophysiology and to develop methods for stratification of patients along the infection-to-sepsis spectrum.

## Methods and analysis

### Study design and settings

This is a multicentre, prospective, observational cohort study conducted across three hospitals in the Netherlands: Amsterdam University Medical Centre and two peripheral hospitals, the Flevo Hospital in Almere and St. Antonius Hospital in Nieuwegein.

### Study population and recruitment

Adult (≥18 years) patients presenting to the ED with suspected or confirmed infection and a MEWS of ≥2 will be screened for eligibility. Components of the MEWS can be found in online supplemental table 1. Lack of informed consent by patients or their legal representative is the only criterion for exclusion. Potential participants will be approached for written informed consent. If a patient is unable or incapable of providing informed consent during the screening process, consent will be sought from the patient’s legal representative. Once the patient is no longer incapacitated, written informed consent will be obtained from the patient.

### Study procedures and follow-up

Samples will be collected in the ED at baseline and, if the patient remains hospitalised, on day 4 (range from 3 to 5). Questionnaires will be administered at 90 days and 1 year following the ED presentation. A summary of the study procedures and sample collection is provided in figure 1. Baseline and clinical data will be collected from the patient’s medical chart until the day of discharge or death. A detailed timeline of the clinical data collected throughout the study is outlined in table 1.

**Table 1 T1:** Data collection timeline

Collected samples and data	Day 0	During admission	3 months	1 year
Plasma, PBMCs, PAXgene samples	X	Day 4		
Rectal swab	X			
Demographics and medical history	X			
Vital parameters	X	Day 4		
Laboratory values	X	Day 4		
Administered medication		X		
Radiology results		X		
Microbiology test		X		
Physician diagnosis	X	Discharge		
Adjudicated diagnoses			X	
Adjudicated complications			X	
Readmission			X	X
Mortality		X	X	X
Postsepsis sequelae			X	X

PBMCs, peripheral blood mononuclear cells.

**Figure 1 F1:**
[figure not shown]
Graphical abstract of the BIOmarkers to diagnose SEPsis (BIOSEP) study. Overview of the study design illustrating the inclusion criteria and the nature and timeline of sample and data collection. MEWS, Modified Early Warning Score; PBMCs, peripheral blood mononuclear cells.

#### Blood sampling and rectal swabs

Blood samples will be collected using ethylenediaminetetraacetic acid (EDTA) tubes for plasma extraction, heparin tubes for isolation of peripheral blood mononuclear cells (PBMCs) and single-cell proteomics using Smart Tubes (Las Vegas, NV, USA) and PAXgene RNA tubes for RNA extraction. The maximum extracted volume of blood will be 67.5 mL at baseline and 57.5 mL at the follow-up visit. Plasma and PAXgene RNA samples will be stored at −70°C and PBMCs at −196°C (liquid nitrogen) in the Amsterdam UMC Biobank.

Rectal swabs (FLOQSwabs 552C, Copan, CA, US) will be collected on day 0 and used for gut microbiota analysis. Rectal swabs are commonly used in clinical practice and are easier to obtain at a specific time point compared with faecal samples.^20^ They have been shown to accurately represent faecal microbiota composition and functionality in both critically ill patients and healthy controls.^21 22^ The swabs are inserted approximately 3 cm into the anal canal by a research team member, healthcare provider or the participant themselves. The swabs will be placed in a container with 500 µL of reduced transport fluid (buffer) and may be kept at room temperature for up to 2 hours before being stored at −70°C.

#### Questionnaires

Approximately 90 days (±2 weeks) and 1 year (±1 month) after presentation to the ED, short questionnaires will be administered. The questionnaires incorporate questions from two validated questionnaires and address mortality, readmission, healthcare use and the sequelae of sepsis.^23 24^ This approach allows us to systematically evaluate the long-term effects of sepsis. The questionnaires are provided in online supplemental material 1.

#### Measurement of immune profiles

The immune response analyses used include mass spectrometry, proteomics, transcriptomics, metabolomics, microbiomics and Raman spectroscopy.

Raman spectroscopy is a non-destructive analytical technique that uses inelastic scattering of light to provide information on chemical composition of samples.^25 26^ Raman spectroscopy will be applied to plasma samples. In this way, it may be able to recognise immunological profiles and identify individuals at high risk of developing sepsis. Host response biomarkers, including those related to coagulation, inflammation and endothelial activation, will be measured in EDTA plasma using Luminex technology. In addition, a proteomic assessment of a broad range of mediators will be conducted using Olink technology (Olink Proteomics, Uppsala, Sweden). Targeted proteomic analysis using Olink technology has been used to identify pathophysiologically relevant alterations in proteins among critically ill sepsis patients.^27^ Furthermore, single-cell proteomics analyses will be performed using mass cytometry, focusing on cell signalling in innate immunity. Gene transcription profiles will be assessed through both whole-blood and single-cell RNA sequencing in a targeted subgroup of patients, using PAXgene tubes and viably frozen PBMCs (Becton-Dickinson, Breda, Netherlands). Identifying transcriptomic endotypes in sepsis patients can provide valuable information about the prognosis of sepsis patients receiving critical care.^15^ A mass spectrometry-based metabolomics platform will be used to assess metabolic profiles in patient plasma. Liquid chromatography-mass spectrometry-based analysis offers opportunity to explore potential sepsis biomarkers.^28^ Microbiota sequencing will be performed. In short, a repeated bead-beating method was used for DNA extraction. 16S ribosomal RNA gene sequencing will be performed on an Illumina system (San Diego, CA, USA) and further preprocessing of sequence data as described.^29 30^

### Current status and protocol changes

Recruitment began on 25 October 2022 and is expected to conclude in 2028. Since the start of recruitment, two amendments have been made to this protocol. In the first amendment, the following changes were made and approved by the METC:

The first follow-up date was changed from day 7 to day 4 and the second follow-up date from day 60 to day 90.The possibility of deferred consent was included in the study for temporarily incapacitated patients.A subgroup of patients for which faeces samples will be collected was defined.The Flevo Hospital was added as an inclusion centre.

In the second amendment, the following changes were made and approved by the METC:

Race and ethnicity were explicitly added as demographic variables to be collected.Follow-up questionnaires were made available for digital use by included patients.The St. Antonius hospital was added as an inclusion centre.

The current version of the original study protocol can be found in online supplemental material 2.

### Study endpoints

The main study parameters will be characterisation of the host immune and metabolic response using multiomics analysis, Raman spectroscopy, mass spectrometry and gut microbiota profiling in relation to clinical outcomes such as 30-day mortality, length of hospital stay, readmission and postsepsis sequelae. The main study parameters and other relevant study variables that will be collected are detailed in table 2.

**Table 2 T2:** Overview of recorded outcomes

Main study parameters	
Host response	Multiomics, Raman spectroscopy, mass spectrometry, gut microbiota analysis
Disease severity	MEWS and SOFA scores
Infection state	Infection diagnosis including causative pathogens and sepsis diagnosis
Mortality rates	In-hospital, 30-day, 90-day and 1-year mortality
Length of stay	Duration of hospital and ICU stay
Readmission	All-cause readmission in the first year after ED presentation
Postsepsis sequelae	Sequelae up to 90 days postadmission

Other relevant study variables	
General demographics	Sex, age, height, weight, race, ethnicity
Medical history	Comorbidities, tobacco, alcohol and drug use, medication use prior to admission
Information prior to ED	Recent surgery, duration of symptoms and antibiotic exposure 3 months prior to ED
Vital signs	Vital signs measured for standard care
Laboratory values	Blood tests conducted as part of standard care
Microbiology tests	Positive cultures, PCR, serology and urine rapid tests for causative microorganisms
Radiology results	Radiology findings positive for infection
Administered medication	Antimicrobials, immunosuppressives, vasopressors and anticoagulants
Organ support	Mechanical ventilation, renal replacement therapy, ECMO, vasopressors
Physician diagnosis	Diagnosis on ED and discharge diagnosis
Complications	AKI, secondary infection, ARDS, myocardial infarction, delirium

* See questionnaires in online supplemental material 1.

AKI, acute kidney injury; ARDS, acute respiratory distress syndrome; ECMO, extracorporeal membrane oxygenation; ED, emergency department; ICU, intensive care unit; MEWS, Modified Early Warning Score; SOFA, sequential organ failure assessment.

### Sepsis and infection definitions

#### Infection diagnosis

In 2013, Klouwenberg *et al* developed and validated a handbook for post hoc adjudication of infection diagnoses in the ICU, which was based on the Centers for Disease Control and Prevention (CDC) surveillance definitions for specific types of infections.^31^ We have updated this handbook using the 2023 CDC surveillance definitions for types of infections.^32^ Additionally, we have expanded it to include common complications of infections and sepsis, including delirium, secondary infections, acute respiratory distress syndrome, acute kidney injury, myocardial infarction, stroke, deep venous thrombosis and pulmonary embolism, based on the most recent versions of consensus definitions.^33^,^38^ Since gold standards are lacking for many infectious diagnoses, it is imperative to use an adjudication system to determine presence and source of infections reliably.^39^

Each patient will be independently reviewed by two experienced physicians, who will use all available data from the medical chart during the admission period. The plausibility of the infection (rated as none, possible, probable or definite), the most likely causative pathogen and sepsis-related complications during the infection period will be assessed based on the diagnostic handbook. In the event of a disagreement between the two reviewers, a third reviewer will evaluate the case independently. If the third reviewer still disagrees with both previous reviewers, a final diagnosis will be made by an independent adjudication committee consisting of specialists in internal medicine. The use of the updated diagnostic handbook in the ED and the interobserver agreement will be evaluated in a separate validation study.

#### Sepsis diagnosis

Sepsis will be defined according to the 2016 Third International Consensus Definitions for Sepsis and Septic Shock (Sepsis-3)^4^ as life-threatening organ dysfunction caused by a dysregulated host response to infection. Organ dysfunction is measured by a change in the SOFA score of ≥2. In cases where prior components of the SOFA score are unavailable, a baseline score of ‘0’ will be assumed. Assessing the pulmonary component can be challenging, since calculating the PaO2/FiO2 ratio requires arterial blood gases, which are not routinely available in the ED. In such cases, we will use a modified SOFA (mSOFA) score which uses the SpO2/FiO2 (SF) ratio as an alternative for assessing respiratory dysfunction. Cut-off values for SF ratios have been validated in large datasets on the ED, ICU and ward.^40^,^43^ Components of the mSOFA score and cut-off values can be found in online supplemental table 2. Sepsis will be adjudicated concurrently with infection diagnoses using the same independent review process.

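### The assumed baseline SOFA of 0 has no exception for documented chronic organ dysfunction, so chronic points can count as acute change and yield a sepsis label

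*Protocol article*

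**What the plan says.** The Sepsis diagnosis section of the Protocol article adopts Sepsis-3 and describes sepsis "as life-threatening organ dysfunction caused by a dysregulated host response to infection". It then makes this operational: "Organ dysfunction is measured by a change in the SOFA score of ≥2". For the starting point of that change it adds: "In cases where prior components of the SOFA score are unavailable, a baseline score of ‘0’ will be assumed". No exception follows for a patient known to have chronic disease of the organ being scored.

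The label is not left to the score alone: "Sepsis will be adjudicated concurrently with infection diagnoses using the same independent review process". Under Infection diagnosis, that process is two physicians, "who will use all available data from the medical chart during the admission period", then a third reviewer if they disagree, then a committee.

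Two other sections bear on who is affected. Chronic organ disease does not bar entry: "Lack of informed consent by patients or their legal representative is the only criterion for exclusion" (Study population and recruitment). Table 2 (Study endpoints) lists the history to be collected, "Comorbidities, tobacco, alcohol and drug use, medication use prior to admission", but nothing links it to the baseline score.

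**The concern.** A missing earlier value does not mean that the organ worked normally before. For a previously healthy patient, zero is a sensible default. For a patient whose history records chronic kidney, liver, lung or haematological disease, it contradicts information the study already holds. If that patient's stable level is worth 2 or more SOFA points and no earlier component can be found, the operational criterion is met without any acute deterioration.

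The label matters because the first objective in the Introduction is "to compare the immune response of patients with and without sepsis presenting to the ED with (suspected) infection", and developing sepsis is the outcome in the second. False cases from this source would have chronic organ disease in common, so they would not be a random sample of non-septic patients. An omics comparison could then report markers of renal, hepatic or pulmonary disease as markers of sepsis.

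**Working it through.** **Reproducing the plan's figures (Sample size).** The pilot sepsis share is 30/279 = 10.75%, stated as 11%. Scaling by 6 gives 279 × 6 = 1674 visits and 30 × 6 = 180 sepsis cases a year. Doubling for MEWS ≥2 gives 2 × 1674 = 3348, against a target of 3300. The figures reproduce. None of them concerns the baseline rule.

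**Number of true cases, T.** The article gives no sepsis rate at MEWS ≥2, so I use two assumptions with N = 3300.
- The patients added by the lower threshold contribute no sepsis: p = 180/3348 = 5.4%, T = 177.
- They have the same rate as the pilot: p = 30/279 = 10.75%, T = 355.

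**Mislabelling rate, q.** Let q be the share of truly non-septic patients labelled septic through the assumed zero, after adjudication has corrected what it will. The documents give no value, so the range is assumed.

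False cases: F = q × (N − T). False share of the labelled sepsis group: F/(T + F).

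| q | F (T = 177) | False share | F (T = 355) | False share |
|---|---|---|---|---|
| 0.5% | 16 | 8% | 15 | 4% |
| 1% | 31 | 15% | 29 | 8% |
| 2% | 62 | 26% | 59 | 14% |
| 5% | 156 | 47% | 147 | 29% |

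For example, at q = 1% and T = 177: 0.01 × (3300 − 177) = 31, and 31/(177 + 31) = 15%. The shares do not depend on N, so the 3330 given in the Abstract leads to the same percentages.

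One labelled case in five is false when F = T/4, that is q = T/[4(N − T)]. This gives 177/(4 × 3123) = 1.4%, or 355/(4 × 2945) = 3.0%. Small rates matter because sepsis is the minority class.

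**These are upper-end figures.** The formula applies q to all non-septic patients. Patients whose infection is adjudicated as none cannot be labelled septic whatever their SOFA score. If q describes only non-septic patients with an adjudicated infection, the base is smaller and so is F.

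**Effect on a biomarker contrast.** Write PPV = T/(T + F), and assume that no true case is missed. Let d be the true mean difference between septic and non-septic patients, and c the mean difference between the falsely labelled patients and the remaining non-septic patients. The observed difference is

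PPV × d + (1 − PPV) × c.

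- If c = 0, this is pure dilution: at q = 1% to 5% the difference shrinks to 0.85–0.53 of its size (T = 177) or 0.92–0.71 (T = 355).
- If d = 0 but c is not, a marker unrelated to sepsis shows a difference of (1 − PPV) × c. At q = 1% and T = 177 that is 15% of the chronic-disease shift.

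Under pure dilution, with an assumed difference of 0.25 SD and two-sided alpha of 0.05, power falls from 0.90 to 0.84 (q = 1%) or 0.63 (q = 5%) at T = 177. At T = 355 it falls only from 0.994 to 0.989 or 0.954.

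**The case against.** The strongest reply is that physicians adjudicate sepsis under a definition that requires dysfunction caused by the response to infection. Two of them read the chart and medical history is collected, so a known dialysis patient need not be called septic on arithmetic alone. This stands in part: adjudication may remove many such cases, and q could be close to zero. As written, it does not close the gap. The article does not say that the assumed zero may be overridden, and it describes the material as chart data from the admission. Escalation needs disagreement, so two physicians applying the same rule would agree on the same wrong label. The planned study of interobserver agreement would not reveal a shared error.

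A second reply is that the adjudication handbook, the full protocol and the modified SOFA table are not shown and may cover this. That is so, and a cross-reference would then settle it. The point, however, is about a rule the article itself states without qualification.

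Third, the study is mainly hypothesis-generating, and relating host response to mortality, length of stay or readmission does not use the sepsis label. This limits the damage to the objectives that do use it.

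A reader might infer three stronger claims, and the documents support none of them. One is that chronic organ dysfunction is labelled as sepsis in general; the zero applies only to unavailable components, and known disease will often come with earlier values. Another is that contamination of the main contrast is established; no data on missing components or chronic SOFA points are given. The third is that the error differs between the academic and the peripheral hospitals; nothing in the article bears on that.

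**Conclusion.** The point holds in limited form. The scoring rule and the definition beside it diverge for one group: patients with documented chronic dysfunction of an organ, no retrievable earlier component, an adjudicated infection, and no correction at adjudication. For them a stated rule can put a wrong label into the contrast of the first objective and the outcome of the second.

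The size is unknown. On the assumed range of 1% to 5% net of adjudication, the false share of labelled cases runs from 8% to 47% across the two case counts, read as upper-end values. A lower q would make it minor. The direction is not fixed either: true differences may be diluted, and chronic-disease markers may appear where sepsis has no effect. The change is worth making because the gap is in the written rule and closing it costs little.

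**What to change.** - Limit the assumed zero to organs with no documented chronic dysfunction.
- Where chronic dysfunction is documented and no earlier value exists, state that adjudicators may use pre-admission records and the comorbidity data to decide whether the component is acute, and have them record that decision.
- Flag every sepsis label that depends on an assumed zero, including cases already adjudicated.
- Repeat the sepsis versus no-sepsis contrast without the flagged cases as a sensitivity analysis. The flagged set will also contain previously healthy patients correctly scored from zero, so this analysis loses true cases and supplements the main contrast; it should not replace it.

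The cost is one extra adjudication field, slightly more adjudicator judgement, back-flagging of completed cases, and one further analysis. The charts are already read twice, the comorbidities are already collected, and recruitment is expected to run to 2028. The flag would also show how many labels rest on the assumption, which is not known now. If the handbook or full protocol already contains such a rule, a sentence pointing to it is enough for the first two items.
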